### Design

This is an international, multi-centre, controlled cluster-randomized trial of a complex intervention. To avoid contamination bias between clinicians in the same service, the unit of randomization and of intervention is the participating healthcare facility.

### Inclusion and exclusion criteria

The hospitals entered the trial in September 2007. The study will be conducted in 46 out of a total of 49 eligible referral hospitals—23 in Mali and 26 in Senegal—spread across both countries. A hospital was eligible for the trial if it had functional operating rooms and carried out more than 800 deliveries annually. Three eligible hospitals were excluded: two already had a structured program for carrying out maternal death audits before the project began, and for one other hospital, written consent was not provided by local authorities. The 46 included hospitals are representative of the existing health system in Senegal and Mali, taking into account the variety of the contexts (urban versus rural) and of the levels of care (primary versus secondary referral health facilities).

The intervention directly targets health professionals involved in obstetric care in the various participating hospitals and, indirectly, the women who give birth in these facilities. These health professionals are the staff who are trained in labour and delivery management and the clinical management of obstetric or neonatal complications: physicians, midwives, obstetric nurses, nurse-anaesthetists, and surgical assistants.

Inclusion criteria for women in the QUARITE study are 1) being a patient who delivered in one of the participating facilities, 2) between September 1, 2007, and August 31, 2011. Exclusion criteria are 1) having delivered at home or 2) in another centre, with postnatal transfer.

### Intervention group activities

These activities started in September 2008 and will end in August 2010. Professionals from the intervention group have been trained in evidence-based practice using the ALARM international course [14] that targets health professionals who provide obstetrical care, reviewing the top maternal killers and suggesting essential tools and problem management with the goal of improving care for mothers and newborns. This course promotes evidence-based practice, using data from up-to-date systematic reviews of randomized trials. The course was developed and is maintained and taught jointly by family physicians, obstetricians, midwives, and nurses from developing countries. It has the administrative support and backing of the SOGC.

The sequence of activities during the two years is directed toward developing local leadership and empowering obstetric teams. To meet this objective, the intervention will be carried out in several steps (Figure 1). The intervention began with recruitment of opinion leaders in each centre and their training in best practices and in maternal death audits (training the trainers). The opinion leaders will then create, in their own centres, obstetric teams charged with implementing the maternal death audits and will organize staff training in best practices with the support of external facilitators (educational outreach visits).

**Figure 1 F1:**
[figure not shown]
**Key steps in the implementation of the ALARM International Program in each hospital of the intervention group**.

a) ***Training opinion leaders***: The local opinion leaders are those responsible for maternity services in the hospitals of the intervention group (one physician and one midwife per centre). In September 2008, the opinion leaders took part in a six-day training session provided by three certified instructors. The session included three days of training in EmOC best practices, one day of training in maternal death audit techniques, one day of awareness training related to economic, sociocultural and ethical barriers (including sexual and reproductive rights), and one day of training in adult education methods. At the end of the session, a normative evaluation was carried out. No financial inducement was given to the health workers involved in the program at the intervention sites.

b) ***Creating and training a multidisciplinary audit committee ***(physicians, midwives, nurses, and administrators), according to the following agenda: 1) identification and training of data collectors on maternal deaths; 2) training of committee members in the process of carrying out audits; and 3) annual summary of audit results.

c) ***Launching the audit cycle***: With the support of external facilitators, the audit process will be set in motion by the audit committee in each centre in accordance with the approach proposed by WHO [15] (see Figure 2). Monthly audit meetings are recommended to analyze cases of maternal deaths in the facility.

**Figure 2 F2:**
[figure not shown]
**Maternal death audit cycle in the hospitals**. Source: Dumont et al [17].

d)***Training qualified staff in best practices***: The local opinion leaders, supported by the external facilitators, will train the professionals in each health facility according to the following agenda: 1) evaluation of needs for best practices training; and 2) organization of between four and eight training sessions in best practices during the intervention period. The themes will be selected by local opinion leaders according to the principal causes of maternal mortality that will be identified during maternal death reviews.

d) ***Educational outreach visits by external facilitators***: A national opinion leader, chosen for his or her expertise and leadership, and the AIP international coordinator will visit all the hospitals in the intervention group every three months. The purpose of these visits will be to support the local opinion leaders in their role of providing AIP training to all the health professionals in the maternity service and to ensure that audits are being carried out, particularly by overseeing an audit meeting. To promote evidence-based practice, meetings with the hospital's professionals and administrators will be encouraged, as well as clinical observation periods related to the themes that were taught.

e) ***Recertification of the opinion leaders***: One year after the initial training (September 2009), the opinion leaders of both countries will undergo an accelerated training session together, led by certified instructors. The purpose of this recertification session is to verify the opinion leaders' knowledge, update them on the clinical content and process of maternal death audits, discuss their roles, share their experiences and confirm their capacity to provide leadership in their clinical settings.

### Control group

No external intervention is planned for this group.

### Study endpoints

Endpoints will be measured including periods before (12 months), during (24 months), and after the intervention (12 months). The main reason for the 12 month pre-intervention data collection was to measure process and outcome indicators during the baseline period and to control the effect of the intervention for possible changes in these indicators within the four-year study period.

The primary endpoint measure is the overall rate of maternal mortality (number of maternal deaths among women giving birth in the facility). The sample size was estimated in order to ensure adequate statistical power to show significant differences in maternal mortality among the groups.

As secondary endpoints, we also defined three levels of measurement for effectiveness of the intervention:

***a) Indicators of resource availability***: A systematic and standardized inventory of available resources will be undertaken each year. The hospital complexity index will be calculated for each facility to reflect the availability of different categories of resources required to provide high quality emergency obstetric care [20]: basic services, screening tests, basic emergency obstetric resources, intrapartum care, general medical services, anaesthesiology resources, human resources, academic resources, and clinical protocols.

***b) Indicators of quality of care***: The clinical data collected will allow us to measure the rates of essential obstetric interventions considered effective in reducing maternal and perinatal mortality: assisted deliveries (forceps and vacuum extraction), caesarean sections, transfusions and hysterectomies, transfers to other heath facilities. The quality of care will also be evaluated on a sampling of cases according to objective criteria for clinical management (criterion-based clinical audit). Repeated satisfaction surveys of the health personnel will allow us to measure, on the one hand, the staff retention rate, and on the other, changes in the level of satisfaction among professionals. Staff movements will be monitored as part of the health workers satisfaction study, for which we undertake an annual census.

***c) Maternal and perinatal health outcomes***: The incidence of maternal mortality will be measured, as well as its distribution among its principal causes: pre- and postpartum hemorrhage, prolonged or dystocic labour, uterine rupture, postpartum infection, pre-eclampsia/eclampsia. We will also measure, in each facility, the case fatality rate, the rate of stillbirths, and early neonatal mortality (during hospitalization). We will monitor referrals in and out of the facilities and track the mortality of mothers and babies discharged from the institutions, using the existing information systems (hospital registers and feedback from referral institutions to the others) and calling the institutions when the information is not available.

Audit of maternal deaths is the cornerstone of this complex intervention. According to WHO [15], audit of maternal deaths should improve inter-personnel communication, team working (and staff motivation), resource availability, performance of health workers, and quality of care. Training for the local opinion leaders and parallel training for other staff in best practices should reinforce the effects of the audit activities on health workers' performance. The other components of the intervention should facilitate the implementation of the program using activities to support the actors (outreach visits). As with other complex interventions, the synergy among all components is expected to be effective. All these effects will ultimately have an impact on maternal mortality (see Figure 3). The effects of each component will be assessed by measuring the process indicators: indicators for the implementation of the program, and indicators of resource availability and of quality of care.

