### Hypotheses

Our hypothesis is that the ALARM International Program (AIP) reduces the overall rate of maternal mortality, as measured in the hospitals in the post-intervention period, by 30% in comparison with the control group. Secondary hypotheses are that the AIP: 1) reduces the number of stillbirths and early neonatal mortality; 2) reduces severe maternal morbidity and the case fatality rate; 3) improves the quality of care through better utilization of local resources and changes in professional practices; and 4) increases the satisfaction of health professionals.

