### Data collection and management

#### Data collection

A system of data collection, independent of the AIP, was set up in September 2007 in the 46 study hospitals. This system is based on the WHO global survey on maternal and perinatal health [20], which considers clinical data at the individual level and organizational data at the facility level. All deliveries carried out in the participating centres are registered by local collectors (nurses or midwives trained to do this). These collectors complete a standard form for each eligible patient that includes information on maternal characteristics, prenatal care, labour and delivery, diagnosed complications, and the vital status of both mother and child at discharge from hospital (see patient registration form, Additional file 1). This information is extracted from the hospital registers and from available medical records whose quality and archiving are regularly monitored by the national coordinator of the study. These data will be collected on an ongoing basis throughout the study. With respect to facility-level data, the national coordinator carries out an annual inventory of the resources available in each hospital using a standardized grid, by visiting all the services of the hospitals involved in EmOC.

To assess the quality of care, we will sample medical records of 50 patients at each of the 46 participating centres using simple random sampling. An external evaluator will assess each record using a criterion-based clinical audit (CBCA) to obtain a score for quality of care. The CBCA scores, ranging from 0 to 27, are then dichotomized as standard (score equal to or greater than 22) versus sub-standard (score below 22) care. The sample size of 50 records/centre will allow us to estimate the proportion of patients receiving standard care in each centre with sufficient precision. Specifically, the half-width of the 95% confidence interval will not exceed 15%. The CBCA developed by the researchers of the QUARITE trial employs evidence-based clinical criteria to ascertain if minimal quality of care is provided to the patients sampled. These criteria have been selected based on thorough review of the literature and expert consensus and are consistent with the WHO guidelines for conducting an obstetrical CBCA (Beyond the numbers: Reviewing maternal deaths and complications to make pregnancy safer. Geneva: World Health Organization, 2004) [15].

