#### Statistical analyses

Binary outcome (maternal death) will be measured for each woman included in the study, while the unit of randomization and intervention is the hospital, to avoid contamination bias. A first descriptive analysis will allow us to verify, in the pre-intervention phase, the comparability of the groups in terms of the characteristics of the centres and of the patients included. The primary analyses will take into account the inter- and intra-cluster variability and adjust the intervention effect for stratification variables (country and hospital type). To adjust the estimate of variance in the intervention's effect on the interdependence of the events measured (maternal death or not) among the patients of a given hospital, we will use the Generalized Estimating Equations (GEE) approach which generalizes logistic regression to cluster data [24]. The interchangeable structure of the residual covariance matrix will be used to represent intra-cluster correlations. In secondary analyses, we will use the multivariable GEE model to adjust the effect of the intervention for those patient-level or hospital-level variables that show a marked imbalance between the two arms of the trial. The same approach will be used for secondary assessment criteria. In all the analyses, the effect of the intervention will be estimated using the odds ratio (95% CI) from the GEE model and tested by one-tailed Wald testing (α = 0.05) [24].

The preliminary analyses will verify whether the intervention's effect varies according to country using the likelihood ratio chi-square test with one degree of freedom for country-intervention interaction. If the test does not reject the null hypothesis at α = 0.05, the interaction will be eliminated from the final model, which will allow us to assess the overall effect of the intervention. On the other hand, if the interactions are statistically significant, the sub-group analyses will assess the effects of the intervention separately for each country, with a power less than 90%. A similar approach will be used to test whether the effect of the intervention depends: (i) on the overall rate of maternal mortality in the pre-intervention phase (Year 1); (ii) on changes in maternal mortality within the intervention period; or (iii) on hospital type.

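### Crude rates of transfusion, hysterectomy and similar interventions, tested one-tailed as quality-of-care indicators, have no stated favourable direction and mix need with provision

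*Protocol article*

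**What the plan says.** - **Hypotheses.** Secondary hypothesis 2 is that the programme "reduces severe maternal morbidity and the case fatality rate". Secondary hypothesis 3 is that it "improves the quality of care through better utilization of local resources and changes in professional practices". Neither carries a numerical effect; the 30% in that section belongs to maternal mortality.
- **Study endpoints, part b.** The first set of quality-of-care indicators will "measure the rates of essential obstetric interventions considered effective in reducing maternal and perinatal mortality". The list is assisted deliveries, then "caesarean sections, transfusions and hysterectomies, transfers to other heath facilities". No denominator and no desired direction is given. The same paragraph adds a criterion-based clinical audit as a further measure of quality.
- **Data collection.** For the audit, "we will sample medical records of 50 patients at each of the 46 participating centres using simple random sampling". Each record is scored from 0 to 27 and classed as standard care at 22 or more. The patient form also records diagnosed complications for every delivery.
- **Statistical analyses.** The primary model is a logistic GEE on maternal death, measured for each woman. On secondary endpoints: "The same approach will be used for secondary assessment criteria". The section then states that all analyses report an odds ratio with a 95% interval and a one-tailed Wald test at 0.05.

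**The concern.** A one-tailed test needs a direction that counts as success. For maternal death the direction is obvious. For these five rates it is not. Calling the interventions effective against mortality hints that more is better, but the article does not say so.

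If the denominator is all women delivered, the rate measures use. Use rises when more women in need are treated, and it also rises when more women are in need. A fall may mean better prevention or poorer provision. Transfusion and hysterectomy respond to severe complications, which hypothesis 2 expects to become rarer, so success on hypotheses 2 and 3 together can leave these rates flat or lower. For caesarean, assisted delivery and transfer the link to hypothesis 2 is weaker, but no favourable direction is fixed for them either.

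What is at stake is how part of the evidence on hypothesis 3 is read. The primary endpoint is not affected.

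**Working it through.** **Figures the plan states.** The sample size concerns maternal mortality only. With 1.5% against 1.055% (odds ratio 0.70), two-sided 0.05, 82% power and design effect 1 + 829 × 0.001 = 1.829, I obtain about 38,471 women against the stated 38,205, so it reproduces. For the audit, the article says that "the half-width of the 95% confidence interval will not exceed 15" per cent. The worst case is 1.96 × √(0.25/50) = 13.9%, which agrees. No power, baseline rate or effect size is stated for the intervention rates, so this point disputes no figure in the plan.

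**Decomposition.** Per woman delivered:

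rate = c × u

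Here c is the share of women who need the intervention and u is the share of those who receive it. The ratio between arms is (c₁/c₀) × (u₁/u₀), and only the second factor describes quality.

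**Illustration.** All inputs are assumptions. In the control arm c₀ = 10% and u₀ = 50%, so the control rate is 5.0%. The ratio does not depend on c₀; the odds ratio depends on it slightly.

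| Intervention arm against control | Rate | Odds ratio | Actual change in care |
|---|---|---|---|
| Need unchanged, coverage 50% → 70% | 10% × 70% = 7.0% | 1.43 | better |
| Need −30%, coverage 50% → 70% | 7% × 70% = 4.9% | 0.98 | better |
| Need −30%, coverage 50% → 60% | 7% × 60% = 4.2% | 0.83 | better |
| Need −30%, coverage unchanged | 7% × 50% = 3.5% | 0.69 | none |
| Need +30%, coverage unchanged | 13% × 50% = 6.5% | 1.32 | none |
| Need +50%, coverage 50% → 40% | 15% × 40% = 6.0% | 1.21 | worse |

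For the second row, (0.049/0.951)/(0.050/0.950) = 0.98. The others follow in the same way.

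An upward test cannot detect the better care in rows 2 and 3 at any sample size, because the true odds ratio is below 1. It would favour rows 5 and 6, where care is unchanged or worse. A downward test would favour row 4, where care is unchanged, and miss row 1, where it is better.

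**Break-even.** To hold the crude rate level when need falls to a fraction r, coverage must rise to u₀/r. From 50%, that is 55.6% (r = 0.9), 62.5% (r = 0.8) or 71.4% (r = 0.7). From 70% with r = 0.7 it is 100%; from 80% with r = 0.7 it would exceed 100%, so the crude rate must fall however good the care.

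**With women in need as denominator,** the six rows read 50% → 70%, 50% → 70%, 50% → 60%, no change, no change, and 50% → 40%. Each then matches the change in care.

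**The case against.** A reader might infer that hypothesis 3 is decided by these rates and that its conclusion would therefore be wrong. The documents do not support this. The criterion-based audit is a second measure of quality, is described at more length, and judges management of the individual case. No rule makes the rates decisive.

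Four further points count against a stronger reading:

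- **Denominator.** The article says only rates. The phrase about each woman included refers to maternal death, and extending the same approach to secondary endpoints carries over the method without expressly fixing a denominator. Per delivery is the natural reading, but it is an inference, and an article may leave the detail to a fuller document.
- **Hypothesis 2.** It speaks of severe morbidity, not of need for interventions. The step is plausible for transfusion and hysterectomy and weak for the other three. It names no 30% fall, so that figure in the table is an assumption.
- **Case mix.** A rise in need common to both arms does not bias the comparison. The rows with more need require a difference between arms. Stratified randomization in size-ranked pairs, the baseline year and the secondary adjustment for marked imbalance all reduce that risk.
- **Reporting.** Odds ratios with 95% intervals are already planned.

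These points limit the concern without removing it. The safeguards address imbalance between hospitals, not a fall in need that the programme itself produces. The one-tailed rule is also fixed for all analyses in the text at hand, so the missing direction is not merely a deferred detail.

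**Conclusion.** The concern holds in limited form. As one of two sets of quality indicators, the five rates are tied to a one-tailed test with no favourable direction given. If they are taken per delivery, those for transfusion and hysterectomy can move against the quality they are meant to show when hypothesis 2 also succeeds. A test on them can miss better care, or read a change in need in one arm as a change in quality.

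The size cannot be derived from the documents. In the illustration, need down 30% and coverage up from 50% to 70% give an odds ratio of 0.98, almost no change. This rests on the per-delivery reading, on need following severe morbidity, and on assumed values for both factors.

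Two conclusions would go too far: that the finding on hypothesis 3 would be wrong, since the audit also informs it, and that no intervention rate can ever bear on quality, since a rate among women with the relevant complication can.

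**What to change.** In Study endpoints (part b) and Statistical analyses:

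1. Name the criterion-based clinical audit as the main measure for the quality-of-care conclusion under hypothesis 3.
2. Analyse the five intervention rates two-sided, with odds ratios and 95% intervals. Report crude rates as utilisation, and say that a rise or fall does not by itself show better or worse quality.
3. Where a rate such as transfusion or hysterectomy is kept as a quality indicator, define it among women with the relevant diagnosed complication, using the existing patient form.

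This changes wording only and needs no new data. The cost is that the quality conclusion leans more on 50 audited records per hospital (50 × 46 = 2,300 in one round). Complication-specific denominators also depend on how complications are diagnosed and recorded, which training could alter in the intervention arm, so these rates should be reported alongside the recorded frequency of each complication by arm.
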